**Methods and analysis:**

A total of 170 eligible patients who meet the Rome IV criteria for refractory IBS will be randomly allocated to receive acupuncture or sham acupuncture. Each patient will receive 12 sessions of acupuncture over 4 weeks and a 4-week follow-up. The primary outcome will be the IBS Symptom Severity Score. Secondary outcomes will include the proportion of participants experiencing adequate relief of global IBS symptoms, the weekly frequency of defecation, the stool properties assessed by the Bristol Grading Scale, the Work and Social Adjustment Scale, the IBS-Quality of Life score, and the Self-Rating Depression Scale and Self-Rating Anxiety Scale anxiety and depression scores. Outcome measures will be collected at baseline, 2 and 4 weeks of the intervention, and 6 and 8 weeks after the intervention. Categorical variables will be compared with Fisher’s exact test or the Wilcoxon rank-sum test, and continuous variables will be compared using Student’s t-test or the Wilcoxon rank-sum test.

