#### Bristol Stool Form Scale

The Bristol Stool Form Scale classifies stool consistency into seven types encompassing complications from constipation to diarrhoea.^23^ In this trial, participants will be asked to record the weekly defecation types and scores. The scores obtained from the Bristol scale will be assessed at baseline and weeks 2, 4, 6 and 8.

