#### Work and Social Adjustment Scale

The Work and Social Adjustment Scale (WSAS) will be assessed at baseline and weeks 2, 4, 6 and 8 using a five-domain scale with a total possible score of 40, with each item scoring from 0 (not affected) to 8 (severely affected). The scale is used to measure problems in functioning with work, home management, social activities, private leisure activities, and family and relationships.^25^

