#### Self-Rating Anxiety Scale and Self-Rating Depression Scale

The majority of patients with IBS have comorbid anxiety and/or depression, which are in turn strongly associated with symptom severity.^27 28^ Hence, anxiety and depression symptoms will be assessed at baseline and weeks 2 and 4 using the Self-Rating Anxiety Scale (SAS) and Self-Rating Depression Scale (SDS). It is noteworthy that SDS >56 will be excluded before the first treatment because of an unstable psychological state or accompanying psychological disorders. According to statistical standards, the total score is multiplied by 1.25 and is then converted into a standardised score ranging from 25 to 100. For SAS, grades 1, 2 and 3 are related to scores of 53–62, 63–72 and >72, respectively.^29^ For SDS, grades 1, 2 and 3 correspond to scores of 50–60, 61–70 and >70, respectively.^30^ Higher scores indicate more severe anxiety and depression.

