### Sample size and statistical analysis

Based on two sample size mean literature data speculation and previous clinical experience,^12 31^ we anticipate the scores of two acupuncture groups on the continuation of current medications as follows: responders can improve refractory IBS on the IBS-SSS with scores of 30 and 15, respectively. The SD is set at 15, and the ratio between the acupuncture and sham acupuncture groups is 1:1. The sample size is calculated with a 20% type II error rate (80% power) and 5% type I error. The superiority trial will be adopted to minimise the difference between the two groups, and a 10-point is expected. In total, a sample size of 154 (77 patients in each group) is estimated. Allowing for 10% loss to follow-up, the sample size expands to 85 patients in each group.

All analyses will be performed using the intent-to-treat (ITT) and the per-protocol (PP) populations. ITT requires all participants to receive a baseline assessment of the primary outcome and at least one acupuncture session or one sham acupuncture administration. Missing values will be imputed through the multiple imputation method. The PP population is usually defined as patients who complete at least 80% of the treatment protocol without major protocol violations. The primary outcome will be assessed using analysis of covariance and adjusted for baseline total IBS-SSS. For other secondary outcomes, continuous variables will be analysed using Student’s t-test or the Wilcoxon rank-sum test, and data will be represented as the mean±SD or median; categorical variables will be calculated using Fisher’s exact test or the Wilcoxon rank-sum test, and data will be presented as frequencies (percentages). In terms of efficacy factors, other covariates, such as age, sex, disease duration, conventional pharmacological agent classification and so on, will be considered for further revision. The differences in blinding and AEs between the groups will be compared using the χ^2^ test. Moreover, we have decided to carry out a subgroup analysis based on patients with IBS subtypes, avoiding a heterogeneous patient population that may affect the efficacy results.

Statistical analysis of all data in this study will be performed by a specialised third-party statistician evaluation. SAS, V.8.2 statistical software (SAS Institute), will be used for data analysis. A two-sided p<0.05 will be considered statistically significant.

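### Continuous secondary outcomes are tested without a baseline covariate although every one is measured at baseline: valid, but inefficient by an amount that depends on the unstated correlation and score type

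*Protocol article*

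**What the plan says.** The section Sample size and statistical analysis fixes two different methods. For IBS-SSS: "The primary outcome will be assessed using analysis of covariance and adjusted for baseline total IBS-SSS". For the rest: "For other secondary outcomes, continuous variables will be analysed using Student’s t-test or the Wilcoxon rank-sum test". The only other sentence on covariates says that "other covariates, such as age, sex, disease duration, conventional pharmacological agent classification and so on, will be considered for further revision". It names no baseline value of any outcome and commits to nothing.

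The Secondary outcomes section gives a baseline assessment for every continuous secondary outcome:

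- Bristol score: "The scores obtained from the Bristol scale will be assessed at baseline and weeks 2, 4, 6 and 8".
- Weekly stool frequency: baseline and the same four later visits.
- WSAS: "will be assessed at baseline and weeks 2, 4, 6 and 8 using a five-domain scale".
- IBS-QOL: baseline and two later assessments.
- SAS and SDS: "anxiety and depression symptoms will be assessed at baseline and weeks 2 and 4".

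The one secondary outcome without a baseline, adequate relief, is a yes/no answer and is not affected.

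The abstract (Methods and analysis) says "The primary outcome will be the IBS Symptom Severity Score" and then, after listing the outcomes, that "continuous variables will be compared using Student’s t-test or the Wilcoxon rank-sum test". It does not mention ANCOVA.

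**The concern.** The plan accepts the case for baseline adjustment on the primary outcome and gives no reason for dropping it elsewhere. A two-group test without the baseline leaves in the error term the part of the between-patient spread that the baseline could explain. Confidence intervals are then wider than they need be for data the trial will already hold.

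This matters here because the Introduction criticises earlier trials for small samples and for lacking social-functioning and psychological measures. WSAS, SAS and SDS answer that criticism, yet they receive the less efficient analysis. The sample size was set on IBS-SSS alone, so no secondary outcome has a demonstrated power margin to spare.

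This is a stated choice of test, not a detail left to an analysis plan. A plan that followed the protocol would inherit it.

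**Working it through.** **Inputs from the protocol.** 77 evaluable patients per arm, 1:1 allocation, two-sided 5% significance level (Sample size and statistical analysis).

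**The plan's own figure.** The 77 per arm does not follow from the stated inputs. With SD 15, 80% power and two-sided 5%, the normal-approximation formula gives 16 per arm for a difference of 15, 36 for a difference of 10, and 142 for a difference of 15 less a margin of 10. That is a separate matter. Here 77 is taken as given, and the relative gains below do not depend on it.

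**Assumptions, not in the documents.** The correlation ρ between baseline and follow-up, taken as 0.3, 0.5 and 0.7; equal SD at both times; a common linear slope in both arms. The protocol does not say whether the t-test is on follow-up or change scores, so both are shown.

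**Error variance, with the follow-up variance set to 1**

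- t-test on follow-up scores: 1
- t-test on change scores: 2(1 − ρ)
- ANCOVA: 1 − ρ²

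**Worth of ANCOVA in patients**

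- against follow-up scores: 1/(1 − ρ²)
- against change scores: 2(1 − ρ)/(1 − ρ²) = 2/(1 + ρ)

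| ρ | 1 − ρ² | 1/(1 − ρ²) | 2/(1 + ρ) |
|---|---|---|---|
| 0.3 | 0.91 | 1.10 | 1.54 |
| 0.5 | 0.75 | 1.33 | 1.33 |
| 0.7 | 0.51 | 1.96 | 1.18 |

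The gain over follow-up scores is therefore about 10%, 33% and 96% more patients; over change scores it is about 54%, 33% and 18%. The order reverses because a change score makes better use of the baseline as ρ rises. At ρ = 0.5 the two t-tests are equally efficient.

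**As power.** The protocol gives no target effect for any secondary outcome, so the benchmark is the effect that a follow-up-score t-test detects with 80% power at 77 per arm: (1.960 + 0.842) × √(2/77) = 0.45 SD. Power for an analysis with error variance v is Φ(0.4515/√(2v/77) − 1.960).

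| ρ | Follow-up t-test | Change-score t-test | ANCOVA |
|---|---|---|---|
| 0.3 | 80.0% | 65.8% | 83.6% |
| 0.5 | 80.0% | 80.0% | 89.9% |
| 0.7 | 80.0% | 95.1% | 97.5% |

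Simulation (4,000 runs per setting) gave ANCOVA power of 83.4%, 90.3% and 97.5%. Under no effect, the follow-up t-test and ANCOVA both rejected in about 5% of runs.

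**The case against.** **The t-test is valid.** This stands. The type I error is held in a 1:1 randomised trial. A reader might infer that omitting the baseline biases the secondary estimates. It does not: chance baseline imbalance adds variance, which the standard error of the test already covers. Only secondary outcomes are affected.

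**The tests may use change scores.** This also stands. The sample-size text describes the anticipated effect on IBS-SSS as an improvement, so change scores are plausible. A reader might take the 96% gain at ρ = 0.7 as the loss in this trial. The documents do not support that: it holds only if follow-up scores are tested, and against change scores the gain at that correlation is 18%. Under these assumptions ANCOVA is still at least as efficient as either test.

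**The gain may be small.** True for follow-up scores at low ρ, about 4 points of power at 0.3. Excluding patients with SDS above 56 narrows the baseline range of that scale and would tend to lower its correlation with follow-up.

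**One model does not suit every outcome.** This stands for the stool outcomes. The Bristol scale runs from constipation to diarrhoea, and the eligibility criteria do not restrict subtype. Improvement can be a rise in one patient and a fall in another, so a mean difference can cancel, and baseline adjustment does not cure that.

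**Covariates are left open.** The sentence on further covariates does not rule out adjustment, but it does not plan adjustment for baseline outcome values either.

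**The abstract.** A reader might infer that it sets a rival primary analysis. Its sentence does not tie the t-test to IBS-SSS and is probably condensation; the methods section states the primary analysis clearly.

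**Conclusion.** The point holds as one of efficiency. Every continuous secondary outcome has a baseline value, and the stated tests include no baseline covariate. The size cannot be read from the documents, because it depends on a correlation and a choice of score that they do not give. Over assumed correlations of 0.3 to 0.7, ANCOVA is worth between 10% and 96% more patients if follow-up scores are tested, and between 54% and 18% more if change scores are tested. These figures compare ANCOVA with the t-test; the rank-sum test was not quantified.

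The case for adjustment is clearest for WSAS, IBS-QOL, SAS and SDS, and weaker for Bristol score and stool frequency. Neither the validity of the secondary tests nor the primary analysis is in question. The change should be made, but the trial does not fail without it.

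**What to change.** 1. **WSAS, IBS-QOL, SAS and SDS:** analyse by ANCOVA with arm and that outcome's own baseline value, reporting the adjusted mean difference with 95% CI. Keep the Wilcoxon rank-sum test as a sensitivity analysis.
2. **Bristol score and stool frequency:** adjust for baseline too, but interpret the result by IBS subtype. The protocol already plans a subgroup analysis by subtype.
3. **Abstract, wording only:** state that IBS-SSS is analysed by baseline-adjusted ANCOVA.

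The cost is a few sentences and one model term per outcome. The baselines are already scheduled, so no visit, patient or measurement is added. The Trial status section places the trial in preparation with no patients yet, so the change can be made before any data could influence it.

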### Blinding assessment

To test the patient-blinding effects, all patients will be asked to guess whether they have received acupuncture or sham acupuncture at the end of the first treatment session and the 12th treatment session.

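### The chi-square comparison of blinding does not say what is tabulated: it points the wrong way if correct guesses are compared, and a non-significant guess-by-arm result cannot show that the blind held

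*Protocol article*

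**What the plan says.** Under Blinding assessment, the protocol article says that "all patients will be asked to guess whether they have received acupuncture or sham acupuncture", and that this happens twice, "at the end of the first treatment session and the 12th treatment session". The stated purpose is to test how well patients were blinded.

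The analysis is given in one sentence under Sample size and statistical analysis: "The differences in blinding and AEs between the groups will be compared using the χ^2^ test". The general threshold in that section is "A two-sided p<0.05 will be considered statistically significant".

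The article does not say whether the tabulated variable is the guess (acupuncture or sham) or whether the guess was right. It names no per-arm estimate or blinding index and states no rule for calling the blind intact or broken.

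**The concern.** The sentence allows two different 2×2 tables. In one, the columns are the guess; in the other, they are correct and incorrect. Because being correct means the opposite guess in the sham arm, moving from one table to the other swaps the two cells of the sham row. The same data can then give opposite results.

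The wording does not settle the choice. The article calls the compared variable blinding, not guess, and pairs it with adverse events, which suggests a rate of successful blinding per arm. The Blinding assessment section, however, defines the datum collected as the guess.

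The primary outcome, the IBS Symptom Severity Score, is rated by the patient, and the acupuncturists are not blinded. The guess is the only check of patient blinding that the article describes. A reader will use it to judge whether a difference between acupuncture and sham could reflect expectation, so the result should be one that can be interpreted.

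**Working it through.** **Inputs from the protocol article**
- Allocation: "the ratio between the acupuncture and sham acupuncture groups is 1:1".
- Arm size: "Allowing for 10% loss to follow-up, the sample size expands to 85 patients in each group", so n = 85 per arm and 170 in total. Before the allowance for loss it is 77 per arm.
- Two-sided 5% level.

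**Assumption.** The article gives no guess rates. Those below are illustrative, and a range is shown. It also gives no numerical figure for the blinding check, so there is none to reproduce.

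**Formulas**
- Pearson chi-square for rows (a, b) and (c, d), without continuity correction: χ² = N(ad − bc)² / [(a+b)(c+d)(a+c)(b+d)].
- Bang index for a two-way guess, in each arm: BI = 2 × (proportion correct) − 1, with standard error 2√[p(1 − p)/n]. Zero is what random guessing gives, +1 is all correct and −1 is all wrong.

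**Case 1: both arms largely identify their treatment (64 of 85 correct in each)**
- Correct by arm, (64, 21) and (64, 21): ad − bc = 0, so χ² = 0 and p = 1.0.
- Guess by arm, (64, 21) and (21, 64): ad − bc = 4096 − 441 = 3655; χ² = 170 × 3655² / 85⁴ = 43.5, p about 4 × 10⁻¹¹.
- BI = 2 × 64/85 − 1 = +0.51 in each arm (95% interval 0.32 to 0.69).

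**Case 2: both arms share the belief that they had acupuncture (68 of 85 in each)**
- Guess by arm, (68, 17) and (68, 17): χ² = 0, p = 1.0.
- Correct by arm, (68, 17) and (17, 68): ad − bc = 4624 − 289 = 4335; χ² = 170 × 4335² / 85⁴ = 61.2, p about 5 × 10⁻¹⁵.
- BI = +0.60 in the acupuncture arm (0.43 to 0.77) and −0.60 in the sham arm (−0.77 to −0.43).

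**Range for case 2.** If a proportion q of both arms guesses acupuncture, the correct-by-arm statistic reduces to 170 × (2q − 1)².

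| q | χ², correct by arm | p |
|---|---|---|
| 0.50 | 0 | 1.0 |
| 0.60 | 6.8 | 0.009 |
| 0.70 | 27.2 | 2 × 10⁻⁷ |
| 0.80 | 61.2 | 5 × 10⁻¹⁵ |
| 1.00 | 170 | 7 × 10⁻³⁹ |

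The 5% critical value of 3.84 is reached at q of about 0.575.

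**Simulation (20,000 trials, 85 per arm, two-sided 5%)**

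| Truth | Guess by arm rejects | Correct by arm rejects |
|---|---|---|
| 80% correct in both arms | 100% | 4.9% |
| 80% guess acupuncture in both arms | 4.9% | 100% |
| 50/50 guessing in both arms | 5.1% | 5.4% |

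For the 80% cases, 77 per arm or a continuity correction leads to the same conclusions.

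**Case 3: guess by arm, not significant.** Suppose 49 of 85 in the acupuncture arm and 37 of 85 in the sham arm guess acupuncture.
- ad − bc = 49 × 48 − 36 × 37 = 1020; χ² = 170 × 1020² / (85 × 85 × 86 × 84) = 3.39, p = 0.066.
- Difference = 0.576 − 0.435 = 0.141; standard error √(0.576 × 0.424/85 + 0.435 × 0.565/85) = 0.076; 95% interval −0.01 to 0.29.
- BI = +0.15 (−0.06 to 0.36) in the acupuncture arm and +0.13 (−0.08 to 0.34) in the sham arm.

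The test does not reject, yet the data are compatible with a difference in guessing of up to 29 percentage points.

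**The case against.** The strongest reply is that the Blinding assessment section defines the datum as the guess. A between-group chi-square on that datum is guess by arm, which behaves correctly in cases 1 and 2. No sentence in the article mentions correct guesses. This stands. A reader might infer that the planned test is bound to pass an unmasked trial and fail a well-masked one, but the article does not support that: it leaves the coding open, and the reversal belongs to only one of the two readings.

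Three related inferences also go too far.
- **A pass/fail rule.** The article says only that differences will be compared. It ties no verdict on blinding to p < 0.05.
- **A false alarm whenever nobody has identified their arm.** This needs a shared lean to one answer. With 50/50 guessing, the correct-guess comparison rejects at about the nominal 5%.
- **A forced choice.** The article lists no response options, so the absence of a *don't know* answer is inferred from silence.

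It can also be said that coding and per-arm reporting are details for a full protocol or analysis plan not shown here, and that the counts behind a chi-square give each arm's guess rate. That is fair as far as it goes and limits the severity. But the article does fix a method, and that method is ambiguous between two tests that can disagree completely. On the favourable reading, its p-value still cannot support a claim that blinding held.

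**Conclusion.** The point holds in a limited form, on either reading of the sentence. If correct guesses are compared, the test points the wrong way: p = 1.0 when 64 of 85 in each arm are correct, and chi-square 61.2 when 68 of 85 in each arm guess acupuncture. If guess by arm is compared, the test of association is valid, but a non-significant result is not evidence of intact blinding (p = 0.066 with an interval reaching 29 points in case 3), and the p-value alone does not describe either arm.

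The figures rest on assumed guess rates and 85 patients per arm. The direction of the results does not depend on the exact rates, except that the false alarm needs a shared lean, of roughly 57.5% or more for chi-square to reach 3.84 when both arms lean equally. The documents do not show which coding is intended. The point is minor: blinding is a supporting check, and the baseline-adjusted analysis of covariance of the primary outcome is unaffected.

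**What to change.** State that the table is guess (acupuncture or sham) by randomised arm. Report it with the Bang blinding index and its 95% confidence interval in each arm, separately for session 1 and session 12, in place of or alongside the chi-square p-value. The pair of indices separates the situations that matter: both clearly positive when patients have identified their arm (+0.60 and +0.60 at 80% correct), opposite signs when both arms share a belief (+0.60 and −0.60), and both near zero under random guessing.

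Two additions are optional. A *don't know* answer could be offered if the form lacks one, though such answers carry less information than a definite guess. Emphasis could also go to the session-1 guess, because by session 12 the guess may reflect how well the patient has done.

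The main change costs one sentence and a routine calculation on data already to be collected. The optional answer would have to be on the case report form before recruitment, and the article describes the trial as still in preparation.

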### Data management and quality control

To guarantee the objectivity of the data, individual participant data will not be disclosed outside. All researchers will receive training regarding data management. Data entry and management will be conducted using a database software clinical trial data management system by data administrators of the China Academy of Chinese Medical Science. An electronic case report form (CRF) will be designed to collect all clinical observation results of each participant before recruitment. The research assistant is responsible for verifying the accuracy and integrity of data to prevent any detection of errors, omissions or items requiring changes or clarification. Data lockup will be implemented by the data administrators on completion of the study. All paper files and electronic data will be kept for 5 years after publication and destroyed thereafter.

To guarantee the quality of this trial, a prespecified SOP, including recruitment and screening of participants, randomisation, laboratory detection results, intervention, details in filling the CRF, assessment of outcomes, data management and AEs of acupuncture, will be unified and trained through a multicentre internal study for consistency of results. Moreover, we will set up a Data and Safety Monitoring Board, an independent advisory group, to review and interpret data generated from the study, and a meeting will be held every 3 months to report the research progress. Each amendment of the protocol will conform to GCP principles and will maintain the ethical standards for RCTs.

### Patients and public involvement

Patients in this trial will not be involved in the design or conduct of the study or the outcome assessments. However, we are planning to disseminate our research to the participants and the public, through means such as publicising our research on hospital social media sites (WeChat subscription) and various academic lectures.

